### **3.8.5. Storage and Management of Investigational Medicinal Products**

#### **3.8.5.1. Storage of Investigational Medicinal Products**

IMPs will be provided free of charge by the sponsor and distributed to each study site as planned. All drugs will be managed by a dedicated drug administrator at the study site to ensure that the drugs can only be used for subjects eligible for inclusion in the clinical study. Distribution of IMPs to non-subjects is prohibited. The monitor will be responsible for monitoring the supply, use, and storage of the clinical IMPs and the disposal of remaining IMPs. IMPs should be stored in a locked drug cabinet as required, under the following storage and transportation conditions: 2-8°C, protected from light.

#### **3.8.5.2. Counting of Drugs**

Clinical study site is responsible for the periodic accountability, quality control and recording of the IMPs. During the study, the investigator or designee must record the quantity of drugs, as well as the missing drugs, i.e., IMPs shall be kept, distributed, received, and recovered by special personnel of the study site. Detailed records are required for the process.

The investigator should ensure the accuracy of IMP count records throughout the study. Use of each dose of IMP will be recorded in the eCRF. The investigator should return all unused or partially used IMP, empty post-use vials to the sponsor after the end of the study and confirm that no remaining drug is left at the study site.

### **3.8.6. Dose Escalation Interruption and Stopping Criteria**

After the completion of the safety observation period following the first dose of IMP for each group of subjects, the severity of AEs will be assessed. The causal relationship of each AE to the IMP will be assessed as described in Section 6.1.4, and AEs that are "definitely related", "probably related" and "possibly related" will be considered related to the IMP. The investigator and the sponsor will decide whether to continue dose escalation of the IMP based

on the safety and tolerability data obtained from all subjects who have completed the previous dose level.

The interruption of dose escalation may be considered if moderate or higher IMP-related AEs with the same system organ class (SOC) are observed in 50% or more of the subjects at that dose level, or if there is an unacceptable AE that the investigator believes is reasonably attributable to the pharmacological effect of the IMP, or if more than 1 subject experiences an SAE in the same SOC, etc.

**If dose escalation is interrupted, the investigator will decide on one of the following solutions after discussion with the sponsor:**

- Continue to escalate to the next dose level as specified in the protocol; or
- Add an intermediate dose or adjust dosing frequency.

**If the interruption of dose escalation occurs for a second time during the study, dose escalation should be stopped.**

Note: AEs definitely due to other reasons will not be considered AEs that meet the interruption and stopping criteria for dose escalation. If any IMP-related SAE occurs during the study, the study needs to be suspended, and the investigator will discuss and analyze the reasons with the sponsor and determine the impact on the subsequent study.

### **3.8.7. Premature Discontinuation of Treatment**

Premature discontinuation of the subject from IMPs is required if any of the following occurs:

- As requested by the subject;
- The subject experiences an intolerable AE related to the IMP as assessed by the investigator;
- The subject experiences any disease that precludes continuation of study treatment, such as any opportunistic infection suggestive of possible immune impairment or other recurrent/long-term infection (as assessed by the investigator) with an abnormal frequency, malignancy (except cervical carcinoma in situ, non-metastatic skin squamous cell carcinoma, and basal cell carcinoma) or serious cardiovascular and cerebrovascular disease;
- The female subject becomes pregnant;
- The subject takes prohibited concomitant medications that leads to discontinuation of IMPs;
- The subject requires early discontinuation of study treatment due to inadequate response;

- The subject has poor compliance with study treatment or protocol requirements;
- The investigator/sponsor decides to discontinue the subject's study treatment.

If a subject discontinues treatment early but does not withdraw from the study, the EOT visit and subsequent follow-up visits should be completed as far as possible. Subjects who discontinue the study treatment prematurely may be replaced following discussion between the investigator and the sponsor.

### **3.8.8. Concomitant Therapies**

All drug therapy (including nutritional supplements) and non-drug therapy received by the subject from the time of signing the ICF until the last visit need to be collected and recorded in the electronic data capture (EDC) system.

To prevent IRRs, all subjects need to receive prophylactic medications before and after each infusion.

Subjects enrolled in this study need to maintain a stable standard of care regimen for at least 30 days before the first dose of IMP. After the subject is randomized and receives the first dose of IMP, the investigator can adjust the standard of care according to the changes in the subject's condition.

#### **3.8.8.1. Standard of Care**

The standard of care regimen refers to the use of any of the following (alone or in combination): corticosteroids, antimalarials, NSAIDs, immunosuppressants or immunomodulators [including azathioprine, mycophenolate (including mycophenolate mofetil, mycophenolic sodium), methotrexate, leflunomide, tacrolimus, ciclosporin].

Antimalarials in the standard of care regimen: hydroxychloroquine maximum dose of 400 mg/day. Quinacrine (Atabrine, Mepacrine) maximum dose of 100 mg/day.

The maximum dose of corticosteroids (equivalent to prednisone dose) in the standard of care regimen is 1 mg/kg/day, and maximal daily dose should be no more than 60 mg/day. For subjects with SLE treated with corticosteroids every other day, the average daily dose of corticosteroids is calculated by taking the average of the 2-day dose.

The maximum dose of azathioprine in the standard of care regimen is 200 mg/day. The maximum dose of mycophenolate mofetil (MMF) is 2 g/day. The maximum dose of methotrexate is 25 mg/week. The maximum dose of ciclosporin is 4 mg/kg/day. The maximum dose of tacrolimus is 0.1 mg/kg/day. The maximum dose of leflunomide is 40 mg/day.

If the subject's clinical condition changes, the standard of care regimen is allowed to be adjusted as needed per the clinical condition, and the reason for adjusting the treatment regimen needs to be recorded.

### **3.8.8.2. Reference for Glucocorticoid Medication**

During the trial, inhaled and topical corticosteroids are allowed to treat diseases other than SLE. The duration of systemic corticosteroid treatment for diseases other than SLE should not exceed 7 days, and the dose should be reduced after 7 days.

When using corticosteroids to treat SLE-related disease activity, please refer to the "2020 Chinese Guidances for the Diagnosis and Treatment of Systemic Lupus Erythematosus" : An individualized hormone therapy regimen should be established according to the type and severity of disease activity and affected organs, and the minimal dose adequate for disease control should be used; for patients with mild active SLE, if hydroxychloroquine or NSAIDs are ineffective, low-dose hormones ( $\leq 10 \text{ mg} \cdot \text{d}^{-1}$  prednisone or other hormones of equivalent dose) may be considered; for patients with moderate active SLE, hormones ( $0.5\text{-}1 \text{ mg} \cdot \text{kg}^{-1} \cdot \text{d}^{-1}$  prednisone or other hormones of equivalent dose) combined with immunosuppressants can be used for treatment; for patients with severe active SLE, hormones ( $\geq 1 \text{ mg} \cdot \text{kg}^{-1} \cdot \text{d}^{-1}$  prednisone or other hormones of equivalent dose) combined with immunosuppressants can be used for treatment, and after the condition is stable, the dose of hormones should be adjusted appropriately; for SLE patients with lupus crisis, hormone pulse combined with immunosuppressants can be used for treatment (hormone pulse therapy is intravenous infusion of methylprednisolone 500-1000 mg/d, usually for 3 consecutive days as a course of treatment, with an interval of 5-30 d between courses. After pulse therapy, oral prednisone  $0.5\text{-}1 \text{ mg} \cdot \text{kg}^{-1} \cdot \text{d}^{-1}$  or other hormones of equivalent dose should be administered, usually for 4-8 weeks, but the specific course of treatment should depend on the condition); clinicians should pay close attention to the disease activity of SLE patients, and adjust the dose of hormones according to the degree of disease activity, and for patients with long-term stable condition, gradual discontinuation of hormones may be considered.

The specific calculation method for the average daily dose of glucocorticoids within 7 days before the visit is the average dose of all glucocorticoids administered intravenously, intramuscularly, orally, and intradermally for the treatment of SLE and non-SLE within 7 days before the visit. If acute exacerbation occurs during the study, the amount of glucocorticoids used in the treatment of acute exacerbation will be included in the calculation of total amount of glucocorticoids.

According to the “Expert Consensus on the Rational Use of Glucocorticoids in Patients with Systemic Lupus Erythematosus” (China, 2014) , during the maintenance treatment period, the dose of glucocorticoids should be slowly reduced at a rate of 10% of the original dose every 1-2 weeks; after the dose is reduced to 0.5 mg·kg·d of prednisone (0.4 mg·kg·d of methylprednisolone), the rate of dose reduction should be appropriately slowed down according to the disease condition.

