| 
 
➤ To explore the preliminary efficacy and some PD characteristics of CM313 after multiple doses.
 
                                                                                                                 | 
 
➤ Preliminary efficacy endpoints: 
 
• Change from baseline in the SELENA-SLEDAI score at each evaluation visit;
 
• Change from baseline in Physician Global Assessment (PGA) score at each evaluation visit;
 
• Time to first SLE flare after randomization;
 
• Change from baseline in prednisone dosage at each evaluation visit;
 
• Change from baseline in the BILAG-2004 score at each evaluation visit;
 
• Changes from baseline in 24-hour protein urine quantification and protein urine/creatinine ratio (only for subjects with protein urine/creatinine ratio exceeding the upper limit of normal during the screening period) at each evaluation visit;
 
• The percentage change from baseline in immunology-related endpoints [immunoglobulin G (IgG), immunoglobulin A (IgA), immunoglobulin M (IgM), immunoglobulin E (IgE), anti-double-stranded deoxyribonucleic acid (ds-DNA) antibodies, complement (C3, C4), C-reactive protein (CRP), and erythrocyte sedimentation rate (ESR) at each evaluation visit.
 
 
 
➤ The expression levels of type I interferon (IFN)-related genes and their changes and rates of change from baseline at each assessment visit.
 
 |

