### 3.8.2.3 Pre- and Post-infusion Medications of Investigational Medicinal Product Infusion Solution

To reduce the risk of IRRs, the following medications are recommended for each subject, before and after each IMP infusion:

Pre-infusion medications (within 1-3 hours before infusion):

- Corticosteroids (intermediate-acting or long-acting): It is recommended to administer 100 mg methylprednisolone (or equivalent drug) intravenously before the 1st and 2nd IMP administrations; starting from the 3rd IMP administration, the corticosteroid dose can be reduced to 60 mg methylprednisolone (or equivalent drug), orally or intravenously. If patients receive the aforementioned methylprednisolone (or equivalent drug) as pre-infusion medication on the IMP administration day, they should not receive additional corticosteroids as part of their standard SLE treatment.
- Paracetamol, 650 mg to 1000 mg, oral.
- Antihistamines: Diphenhydramine, 25 mg to 50 mg (or equivalent), oral or intramuscular.

Post-infusion medications:

- Starting from the day after the completion of the infusion, subjects should receive corticosteroids for 2 consecutive days (20 mg methylprednisolone or equivalent drug daily). If the oral corticosteroid dose in the subject's standard SLE treatment is  $\geq$  the above dose, no additional corticosteroids will be given; if the oral corticosteroid dose in the subject's standard SLE treatment is  $<$  the above dose, corticosteroids will be supplemented to the above dose).
- In addition, for subjects with a history of chronic obstructive pulmonary disease (COPD), post-infusion medications may be considered, including short-acting and long-acting bronchodilators and inhaled corticosteroids.

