### 8.2. Analysis Sets

**Full Analysis Set (FAS):** It includes all randomized subjects who have received at least one dose of IMP.

**Per-Protocol Set (PPS):** It is a subset of the FAS, including all subjects in the study who complete treatment with IMP as required by the protocol, have no major protocol deviations, and have available efficacy endpoints, and do not affect the efficacy evaluation. The PPS should satisfy at least the following criteria:

- Meeting the inclusion criteria specified in the study protocol;
- Meeting no exclusion criteria specified in the study protocol;
- Receiving no medications or treatments that may affect the efficacy evaluation during the study;
- Good compliance.

**PK Concentration Set for the First Dose (PKCS1):** It includes all subjects who have completed the first dose of IMP and have at least one valid post-first dose concentration data.

**PK Parameter Set for the First Dose (PKPS1):** It includes all subjects who have completed the first dose of IMP and have at least one valid post-first dose PK parameter.

**PK Concentration Set for the Last Dose (PKCS2):** It includes all subjects who have completed all doses of IMP and have at least one valid post-last dose concentration data.

**PK Parameter Set for the Last Dose (PKPS2):** It includes all subjects who have completed all doses of IMP and have at least one valid post-last dose PK parameter.

**PD Set (PDS):** It includes all subjects who have received at least one dose of IMP and have one valid PD data.

**Immunogenicity Set (IMGS):** It includes all subjects who have received at least one dose of IMP and have one valid post-dose immunogenicity data.

**Safety Set (SS):** It includes all subjects who have received at least one dose of IMP.

The above analysis sets will be discussed and decided jointly by the principal investigator, sponsor, statistician and data management personnel in the blind data review meeting before database lock.

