| 
... A change in SELENA-SLEDAI score of 3 points or more (but not exceeding 12 points)
 
... New/worsening:
 
 
Deep photo-sensitive discoid erythema
 
Cutaneous vasculitis and blisters
 
Nasopharyngeal ulcer
 
Pleurisy
 
Pericarditis
 
Arthritis
 
Pyrexia (due to SLE disease activity)
 
 
... Prednisone dose increased, but not exceeding 0.5 mg/kg/day
 
... NSAIDs or hydroxychloroquine added for active SLE
 
... An increase of 1.0 or more, but no more than 2.5, in PGA score
 | 
... SELENA-SLEDAI score change greater than 12
 
... New/worsening:
 
 
Central nervous system manifestations—systemic lupus erythematosus
 
Vasculitis
 
Nephritis
 
Myositis
 
Platelet count < 60,000
 
Hemolytic anaemia: hemoglobin < 70 g/L or a decrease in hemoglobin > 30 g/L
 
 
Require: Double the dose of prednisone, or increase prednisone to >0.5 mg/kg/day, or hospitalisation
 
... Prednisone increased to >0.5 mg/kg/day
 
... New cyclophosphamide, azathioprine, methotrexate, and mycophenolate used for active SLE
 
... Hospitalization due to active SLE
 
... Physician Global Assessment score (PGA score) increased by > 2.5
 |

Source: [1] Petri M, Kim MY, Kalunian KC, et al. Combined oral contraceptives in women with systemic lupus erythematosus. N Engl J Med. 2005;353 (suppl): 2550 - 2558.

[2] Jill P Buyon, Michelle A Petri, Mimi Y Kim, et al. The effect of combined estrogen and progesterone hormone replacement therapy on disease activity in systemic lupus erythematosus: a randomized trial. Ann Intern Med. 2005 Jun 21;142(12 Pt 1):953-62.

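### Section 3.8.8.2 does not exclude infusion steroid, which raises the prednisone endpoint at V3 and V7 to V10; separately, premedication literally meets Appendix 3's severe-flare steroid line

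*Protocol*

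**What the plan says.** Section 2 lists among the exploratory efficacy endpoints "Change from baseline in prednisone dosage at each evaluation visit", and section 5.3.4 has the dosage recorded at every visit from V1 to V14 as an indicator of SLE outcome. The only pre-visit calculation in the protocol is in section 3.8.8.2: the "average dose of all glucocorticoids administered intravenously, intramuscularly, orally, and intradermally for the treatment of SLE and non-SLE", taken over the 7 days before the visit. That section adds that steroid for an acute exacerbation is counted. It excludes nothing.

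Section 3.8.2.3 attaches steroid to every infusion:

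- Doses 1 and 2: "It is recommended to administer 100 mg methylprednisolone (or equivalent drug) intravenously before the 1st and 2nd IMP administrations".
- Doses 3 to 5: "starting from the 3rd IMP administration, the corticosteroid dose can be reduced to 60 mg methylprednisolone (or equivalent drug), orally or intravenously".
- Subjects given this on an infusion day: "they should not receive additional corticosteroids as part of their standard SLE treatment".
- The next two days: topped up to 20 mg/day methylprednisolone if the background dose is lower.

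The Synopsis and section 3.8.2.3 call these medications recommended. Section 3.8.8 says that all subjects need them.

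Appendix 3 has two stand-alone steroid lines. One, for mild or moderate flare, is "Prednisone dose increased, but not exceeding 0.5 mg/kg/day". The other, for severe flare, is an increase to above 0.5 mg/kg/day. Neither gives a reason for the increase, whereas the lines on NSAIDs or hydroxychloroquine, on new immunosuppressants and on hospitalization all require active SLE.

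**The concern.** The baseline value is taken before the first infusion and contains no infusion steroid. Values in the week after an infusion do contain it. The change from baseline at those visits would then partly measure the premedication schedule, and a real reduction in lupus steroid could be hidden at them, including at EOT.

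The flare problem is separate and comes from Appendix 3 alone. If the steroid lines are scored as written, premedication on D1 counts as a flare in both arms, and the Kaplan-Meier estimate of time to first flare carries no information. Sections 5.3.2 and Table 1 ask for the number, severity and date of flares, not for the item that triggered each one. A later analysis plan could not reliably undo such scoring from those fields.

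**Working it through.** The protocol gives no figure of its own to reproduce, so the rule is applied directly.

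**Inputs**

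- Conversion: section 3.8.8.2 equates 0.5 mg/kg prednisone with 0.4 mg/kg methylprednisolone, so the factor is 0.5/0.4 = 1.25.
- Pre-infusion dose P: 100 × 1.25 = 125 mg (doses 1 and 2); 60 × 1.25 = 75 mg (doses 3 to 5).
- Two days after: the larger of the background B and 20 × 1.25 = 25 mg.
- Infusions on D1, D29, D36, D43 and D50 (Table 1).
- Background B: 0 up to the 60 mg/day ceiling of section 3.8.8.1.
- Assumptions: B is constant, visits fall on nominal days, the averaging window is the seven days ending the day before the visit, premedication is given, and the permitted reduction from dose 3 is used.

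**Seven-day mean after an infusion**

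Mean = [P + 2 × max(B, 25) + 4B] / 7

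| Background B (mg/day) | V3, V7 mean | Change | V8, V9, V10 mean | Change |
|---|---|---|---|---|
| 0 | (125+50+0)/7 = 25.0 | +25.0 | (75+50+0)/7 = 17.9 | +17.9 |
| 10 | (125+50+40)/7 = 30.7 | +20.7 | (75+50+40)/7 = 23.6 | +13.6 |
| 20 | (125+50+80)/7 = 36.4 | +16.4 | (75+50+80)/7 = 29.3 | +9.3 |
| 60 | (125+120+240)/7 = 69.3 | +9.3 | (75+120+240)/7 = 62.1 | +2.1 |

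At V4 to V6 and V11 to V14 no infusion day or top-up day falls in the window, so the change is 0. The rise appears at 5 of 12 post-baseline visits.

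**Sensitivity**

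- With V3 on D9, the infusion day leaves the window. The rise is 2 × (25 − B)/7, which is 7.1 at B = 0, 4.3 at B = 10, and 0 at 25 mg or more.
- With V7 on D35 and V8 on D44, only one top-up day remains. The rise is (25 − B)/7, which is 3.6, 2.1, and 0 at 25 mg or more.
- A taper can cancel the V8 rise: from 60 to 57 mg/day the mean is (75 + 6 × 57)/7 = 59.6; from 40 to 34 it is (75 + 6 × 34)/7 = 39.9.
- If the reduction from dose 3 is not used, V8 to V10 take the V3/V7 values.

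**Appendix 3, single-day dose**

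At 60 kg (assumed), 125/60 = 2.08 mg/kg and 75/60 = 1.25 mg/kg. The 0.5 mg/kg line is exceeded below 125/0.5 = 250 kg and 75/0.5 = 150 kg respectively.

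**Appendix 3, 7-day mean**

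Of the five affected visits, only V8 and V10 are flare-assessment visits. At 60 kg the mean there is 17.9/60 = 0.30 mg/kg (B = 0), 23.6/60 = 0.39 (B = 10) and 29.3/60 = 0.49 (B = 20), all below the severe line. At 50 kg and B = 20 it is 29.3/50 = 0.59, above it.

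**The case against.** The link from the 7-day rule to the endpoint is inferred. The rule sits in a reference section on concomitant steroid, the endpoint sections say only prednisone dosage, and section 8 leaves detailed analysis to an SAP that is not shown. That stands as a limit on certainty. It does not remove the point, because no other pre-visit calculation exists and section 5.3.4 explains the endpoint in terms of glucocorticoid dosage.

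The rule speaks of treatment of SLE and non-SLE, while section 3.8.8 calls the infusion drugs prophylactic. Leaving prophylaxis out is therefore a possible reading. This too stands, but it means that sites could apply the rule in two ways.

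On flares, section 5.3.2 says that the index serves to detect SLE flares, and a sensible investigator would not score premedication in a stable subject. That is fair, but Appendix 3 qualifies the neighbouring lines and not these two.

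Section 3.8.8.4 already has dose, dates and indication recorded for each concomitant therapy, so the prednisone values could be recomputed. That lowers the severity. It does not help with flares already scored at site.

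A reader might also infer that the per-protocol criterion "Receiving no medications or treatments that may affect the efficacy evaluation during the study" would disqualify everyone who had infusion steroid. Section 8.2 does not support this: it defines the set by treatment completed as the protocol requires, without major deviations, and membership is settled at blind review.

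**Conclusion.** The point holds as a moderate one. Applied as written, section 3.8.8.2 adds 9.3 to 25.0 mg/day at V3 and V7 and 2.1 to 17.9 mg/day at V8 to V10, for backgrounds from 60 down to 0 mg/day. This rests on the inferred link to the endpoint, a stable background, the nominal schedule, and premedication being given. Independently of that rule, the single-day pre-infusion dose literally meets the severe-flare steroid line from D1.

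Three stronger readings are tempting and not supported:

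- **That the endpoint rises in every subject throughout.** The artefact is zero at seven of twelve post-baseline visits, and visit windows or a taper can remove it at higher backgrounds.
- **That the V3 and V7 averages trigger a severe flare.** Neither is a flare-assessment visit, nothing applies the 7-day mean to Appendix 3, and the 25.0 mg mean at zero background lies below the 30 mg that 0.5 mg/kg represents at 60 kg.
- **That one arm is favoured.** Both arms get the same premedication, so the rise does not by itself do so. Stopping infusions early would, however, look like a steroid reduction.

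Both affected endpoints are exploratory. The primary safety endpoint is untouched.

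**What to change.** **Section 3.8.8.2.** State that the prednisone endpoint uses this 7-day average with the pre- and post-infusion steroid of section 3.8.2.3 excluded, flagged by indication in the eCRF. State also that infusion days are left out of the average (or counted at the prescribed background dose) and that the two following days are counted at the background dose. Without this, exclusion creates its own error: background steroid is withheld on the infusion day, so the mean becomes 6B/7, a false fall of B/7. That is 20/7 = 2.9 mg/day at 20 mg and 60/7 = 8.6 at 60 mg. With it, a stable background gives a change of 0 at every visit.

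**Appendix 3.** Add a scoring note that the two stand-alone steroid lines count only increases prescribed for active SLE. Do this before flare scoring begins.

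**Premedication status.** The Synopsis and section 3.8.2.3 (recommended) must be reconciled with section 3.8.8 (needed by all subjects).

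The cost is protocol wording and one eCRF flag. The indication of each concomitant therapy is already collected, and no treatment changes.
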